##### Objective 2: comparison timing of treatment, regardless of treatment type

The effect of timing of PTSD treatment on the primary outcome will be evaluated (simultaneous vs sequential) with (G)LMMs. Baseline CAPS-5 score will be included as covariate and timing of treatment as fixed effect. Overall effects will be evaluated, as well as between-group differences at separate follow-up time points (6-months and 9-months after baseline), by adding time and an interaction between group and time to the model. The intercept will be treated as a random effect.

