### Current study

This paper describes the study design of the Treatment Of PTSD and Addiction (TOPA) study, a Dutch RCT in patients with co-occurring PTSD and SUD who will receive PTSD treatment as an add-on to regular SUD treatment.

The primary objectives of this study are:
To compare effectiveness of PE, EMDR, and ImRs as add-on to regular SUD treatment with SUD treatment only in patients with co-occurring PTSD/SUD.To compare effectiveness of simultaneous SUD/PTSD treatment with sequential SUD/PTSD treatment in patients with co-occurring PTSD/SUD.To explore differential effectiveness between active PTSD treatments (PE vs. EMDR; PE vs. ImRs, EMDR vs. ImRs) in patients with co-occurring PTSD/SUD.

We expect that at 3-month follow-up, all trauma focused therapies will have led to a stronger reduction of the primary outcome PTSD symptoms than the SUD treatment only condition (objective 1). In addition, we expect that, compared to the SUD treatment only condition, all trauma focused therapies will have led to a stronger reduction of the following secondary outcomes: psychological distress, substance use, interpersonal problems, emotion dysregulation, guilt, shame and anger. We expect a greater reduction of PTSD symptoms in the simultaneous treatment condition compared to the sequential treatment condition at 6 and 9-month follow-up (objective 2). We have no specific hypothesis about the direction of the differences in effectiveness between the three active PTSD treatments (objective 3).

Due to the COVID-19 outbreak in March 2020, temporary changes in both treatment as well as assessments had to be made, as the regular face-to-face contacts were temporarily not allowed at the treatment facility center where this study is conducted. In this article the original design of the study is described in the method section. At the end of the method section, all adjustments that were made due to COVID-19 outbreak are described.

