## Methods

### Design

This study is a single blind 6-arm randomized controlled trial, consisting of 3 arms for simultaneous SUD/PTSD treatment with the PTSD treatments consisting of PE, EMDR, and ImRs, and 3 arms for sequential SUD/PTSD treatment with the PTSD treatments also consisting of PE, EMDR, and ImRs. Within the first 3 months after baseline, the three sequential treatment arms together form the SUD treatment only condition, as is depicted in the trial flow (Fig. 1). First, patients are randomly allocated to simultaneous PE, EMDR, or ImRs, or the SUD treatment only group. Subsequently, patients in this last group are randomly allocated to sequential PE, EMDR, or ImRs. The study is conducted at two departments of Jellinek. Jellinek is a Dutch addiction treatment facility center, offering both intramural and extramural addiction treatment. The duration of the study is planned to be 3.5 years, from inclusion of the first participant until the last follow-up measure of the final participant. The research protocol has been approved by the Medical Ethical Committee of the Amsterdam Academic Medical Centre (AMC) and the trial has been pre-registered at the Netherlands Trial Register (NTR L7885). The study is currently running.

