#### Randomization and procedure

After the baseline assessment (T0), patients are randomly assigned to PE, EMDR, ImRs or SUD treatment only (each 25% chance). All patients receive SUD treatment shortly after the baseline assessment. Patients allocated to PE, EMDR or ImRs receive PTSD and SUD treatment simultaneously (75% of the sample), whereas patients in the 3-month SUD treatment only condition receive PTSD treatment after completing 3 months SUD treatment (25% of the sample). Patients in the SUD treatment only condition are randomly allocated to either PE (33% chance), EMDR (33% chance) or ImRs (33% chance) and start with the PTSD treatment after the 3 months follow-up assessment (T1).

After randomization, only disclosure of the timing will be given to the participants. Disclosure of treatment type will be done by the therapist at the start of the first session of the PTSD treatment.

Randomization is carried out by an independent researcher from Arkin who uses a computer-generated block randomization schedule. First patients are allocated to: simultaneous PE, simultaneous EMDR, simultaneous ImRs of sequential treatment with allocation probabilities per condition of 1/4. Block sizes are 4 and 8. Second, participants randomized to sequential treatment are allocated to: sequential PE, sequential EMDR or sequential ImRs, with allocation probabilities per condition of 1/3, after completion of the 3-months follow-up (T1) assessment. Block sizes are 3 and 6. Randomization is stratified by type of care (inpatient, daytreatment or outpatient) and location (Amsterdam or Utrecht). To prevent selection bias, all researchers are blind to order of block size and will not have access to the randomization schedule.

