#### Assessments

Assessments take place at baseline (T0), after 3 months (T1), 6 months (T2) and 9 months (T3). The T0 takes place within 1–2 weeks before the start of SUD treatment. Therefore, participants randomized to simultaneous SUD/PTSD treatment will receive PTSD treatment between baseline (T0) and 3-month follow-up (T1), whereas participants randomized to sequential SUD/PTSD treatment will receive PTSD treatment between 3-month (T1) and 6-month (T2) follow up. See also the flow chart in Fig. 1. All assessments are conducted by a junior researcher (MSc in Psychology), who is blind to treatment condition. In case of unblinding during an intermittent measurement, another assessor will administer the next measurement(s). All assessments consist of a 45–60 min interview-administered instrument to measure severity of PTSD symptoms (CAPS-5) and several self-report questionnaires. In total, assessments take 90–120 min to administer. All participants receive a gift voucher of €15 for each assessments to acknowledge the time and effort they provide in participating in the research. The self-report questionnaires that are administered are described in the following section and listed in Table 1.

**Table 1 Tab1:** Measurement instruments at every measurement moment

	Screening measurement	T0	T1	T2	T3

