#### Primary outcome measure

The primary outcome measure will be the continuous variable PTSD symptom severity, as measured with the CAPS-5 at all follow-up assessments. Additionally, based on the same CAPS-5 assessments we will evaluate the dichotomous variables loss of PTSD diagnosis (no longer meeting criteria for PTSD) and full remission of PTSD (CAPS-5 score < 20), as these dichotomous variables are easy to interpret and are needed to calculate the number needed to treat. Most secondary outcome measures are continuous variables, with the exception of treatment completion of PTSD treatment and completion of SUD treatment, which are dichotomous variables.

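### Objective 2's overall timing effect has no stated window and, read literally, includes the 3-month visit, when the sequential group has not yet had PTSD treatment

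*Protocol article*

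**What the plan says.** All references are to the protocol article.

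- **Outcome.** Under Data analyses, Primary outcome measure, the outcome is "PTSD symptom severity, as measured with the CAPS-5 at all follow-up assessments". Under Assessments: "Assessments take place at baseline (T0), after 3 months (T1), 6 months (T2) and 9 months (T3". Baseline CAPS-5 is a covariate, so the follow-ups available as outcomes are T1, T2 and T3.
- **Objective 2 analysis.** "The effect of timing of PTSD treatment on the primary outcome will be evaluated (simultaneous vs sequential) with (G)LMMs". Then: "Overall effects will be evaluated, as well as between-group differences at separate follow-up time points (6-months and 9-months after baseline". The model has a random intercept; time and a group-by-time interaction are added for the separate time points.
- **Objective 2 hypothesis** (Current study): a "greater reduction of PTSD symptoms in the simultaneous treatment condition compared to the sequential treatment condition at 6 and 9-month follow-up (objective 2").
- **Status of the sequential group at T1.** Under Randomization and procedure, these patients "start with the PTSD treatment after the 3 months follow-up assessment (T1"). Under Design: "Within the first 3 months after baseline, the three sequential treatment arms together form the SUD treatment only condition".
- **Expected T1 result** (Current study): "all trauma focused therapies will have led to a stronger reduction of the primary outcome PTSD symptoms than the SUD treatment only condition (objective 1").

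**The concern.** The Objective 2 paragraph names two kinds of result: an overall effect and effects at separate visits. Only the second has a time window. The overall effect takes its window from the definition of the primary outcome, which covers every follow-up and is nowhere narrowed to leave out T1.

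T1 does not bear on the timing hypothesis. At that visit the simultaneous arms have had their PTSD treatment period and the sequential arms have not started theirs. The difference there shows whether PTSD treatment works, which Objective 1 already tests and which the sponsor expects to favour treatment. Averaging it into the overall timing effect pulls the estimate towards simultaneous treatment, the direction that Objective 2 predicts, even if the groups are the same once both have been treated.

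Timing is one of the three primary objectives, and the Conclusion section expects the findings to improve guidelines. The section on secondary study parameters says that those outcomes follow the same analyses, so the open window carries over to them.

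**Working it through.** **Inputs from the Sample size section.** n = 41 sequential and 121 simultaneous; within-person correlation ρ = 0.60; alpha = 0.05 (two-sided is my assumption).

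**The plan's own timing power.** For a repeated-measures group-by-time test with two groups and two measurements, the noncentrality is λ = f²·N·m/(1−ρ), with N = 162, m = 2 and 1 and 160 degrees of freedom.
- f = 0.15: λ = 0.0225 × 162 × 2 / 0.4 = 18.2, power 98.9% (stated 99%).
- f = 0.10: λ = 0.01 × 162 × 2 / 0.4 = 8.1, power 80.8% (stated 81%).

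Both figures reproduce. They concern a single pre-post change, so they do not show which visits the overall effect covers.

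**Assumptions for the check.** Outcome SD is 1 at each visit, all pairwise correlations are 0.60, data are complete and visits have equal weight. With complete data, the group effect of the random-intercept model is then the baseline-adjusted difference in the mean of the modelled follow-ups. The true group difference is d at T1 and zero at T2 and T3.

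**Standard error of the overall effect.**
- Residual variance after baseline adjustment: 1 − 0.60² = 0.64.
- Residual correlation between follow-ups: (0.60 − 0.36)/0.64 = 0.375.
- Group-size factor: √(1/41 + 1/121) = 0.1807.
- T1 to T3: SD of the mean = √(0.64 × (1 + 2 × 0.375)/3) = 0.611; SE = 0.611 × 0.1807 = 0.110.
- T2 and T3 only: SD of the mean = √(0.64 × (1 + 0.375)/2) = 0.663; SE = 0.663 × 0.1807 = 0.120.

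**Shift and rejection rate.** The T1-T3 average is shifted by (d + 0 + 0)/3 = d/3. The two-sided rejection rate is 1 − Φ(1.96 − z) + Φ(−1.96 − z), with z = (d/3)/0.1104. The document gives no value for d, so a range is shown.

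| Assumed T1 gap d (SD) | Shift d/3 (SD) | z | Rejection at nominal 5% |
|---|---|---|---|
| 0.2 | 0.07 | 0.60 | 9% |
| 0.3 | 0.10 | 0.91 | 15% |
| 0.5 | 0.17 | 1.51 | 33% |
| 0.6 | 0.20 | 1.81 | 44% |
| 0.8 | 0.27 | 2.42 | 68% |

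Nearly all of these rejections favour simultaneous treatment. For T2 and T3 only, the shift is zero and the rate is 5% at every d.

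**Sensitivity.**
- All 204 patients analysed, 51 versus 153: 10%, 17%, 39% and 77% for d = 0.2, 0.3, 0.5 and 0.8.
- Follow-up correlation 0.8 with d = 0.6: 34% instead of 44%.
- Simulation of the baseline-adjusted visit mean (20,000 trials per setting): about 15% at d = 0.3, 43-44% at d = 0.6, and about 5% with no gap or with T2 and T3 only.
- Dropout after T1 would give T1 more than one-third of the weight and enlarge the shift.

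**The case against.** The strongest reply is that the Objective 2 paragraph never mentions T1 or 3 months. The only visits it names are 6 and 9 months, and the parallel sentence under Objective 3 has no such bracket, so it was added specifically for timing. The hypothesis has the same window. The general outcome definition does not settle the matter alone, since Objective 1 uses T1 only under that definition. A model with T2 and T3 as its only outcomes fits all of this. That stands: a reader might infer that the plan definitely puts T1 into the timing test, and the document does not support so firm a statement. It does not exclude T1 either, and the literal text brings it in.

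A reader might also infer that the whole of Objective 2 is compromised. It is not. The 6- and 9-month contrasts are pre-stated, match the hypothesis and are untouched. However, the overall effect is named first and nothing ranks it below them.

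A T1-T3 average can be defended under intention to treat as total symptom burden over nine months, since earlier relief is a real consequence of starting earlier. As a description, that stands. It is a different quantity from the stated hypothesis, and it reuses Objective 1's contrast.

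Finally, an article may leave the exact contrast to a fuller document. Silence would be no fault. Here, though, the article names an overall effect on an outcome whose stated window is wider than the hypothesis.

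**Conclusion.** The point holds as an undefined window whose literal reading conflicts with the hypothesis. It is not a proven error in the timing analysis, and it should be fixed before the data are analysed. If T1 is included, the overall timing effect is shifted by one-third of the T1 gap when there is no true difference at T2 and T3, and the 5% test rejects in about 9% to 68% of trials. Those rates depend on the assumed gaps of 0.2 to 0.8 SD, equal visit weights, complete data, a correlation of 0.60 and analysed groups of 41 and 121. The one-third follows from equal weighting of three visits and does not depend on the size of the gap. If the authors meant T2 and T3 only, the shift is zero and the point reduces to stating so.

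**What to change.** State that the overall timing effect is the average of the T2 and T3 group differences, for CAPS-5 and for secondary outcomes analysed the same way. T1 may stay in the model as a repeated measure with its own group-by-time term, provided it does not enter the timing contrast; the T1 difference is then reported under Objective 1. If a T1-T3 average is also wanted, label it as total symptom burden and do not use it to test the timing hypothesis.

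The cost is one sentence and a changed contrast statement, with no extra data. The overall contrast averages two visits instead of three, so its standard error rises from about 0.110 to 0.120 SD (0.1199/0.1104 = 1.09, about 9%).

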##### Objective 3: head-to-head comparison PTSD treatments, regardless of timing of treatment

The 3 treatment conditions will be compared head-to-head (PE vs EMDR; PE vs ImRs; EMDR vs ImRs) with (G)LMMs. Baseline CAPS-5 score will be included as covariate and treatment type as a fixed effect. Overall effects will be evaluated, as well as between-group differences at separate follow-up time points, by adding time and an interaction between group and time to the model. The intercept will be treated as a random effect.

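### Objective 3 does not exclude 3-month scores of sequential patients, who then have no PTSD-treatment type, so its T1 type contrast is diluted by a quarter

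*Protocol article*

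**What the plan says.** The section heading sets the pooling: "Objective 3: head-to-head comparison PTSD treatments, regardless of timing of treatment". On the model it says "Baseline CAPS-5 score will be included as covariate and treatment type as a fixed effect", and then "Overall effects will be evaluated, as well as between-group differences at separate follow-up time points, by adding time" and a group-by-time interaction, with a random intercept. It has no term for simultaneous versus sequential treatment and names no visits.

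The visits are defined elsewhere. Under Assessments: "Assessments take place at baseline (T0), after 3 months (T1), 6 months (T2) and 9 months (T3"). Under Data analyses, Primary outcome measure, the outcome is CAPS-5 severity "as measured with the CAPS-5 at all follow-up assessments". The parallel text for Objective 2 does restrict its visits: "between-group differences at separate follow-up time points (6-months and 9-months after baseline").

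Under Randomization and procedure, sequential patients are allocated to a type "with allocation probabilities per condition of 1/3, after completion of the 3-months follow-up (T1) assessment". Under Assessments, "participants randomized to sequential SUD/PTSD treatment will receive PTSD treatment between 3-month (T1) and 6-month (T2) follow up". The Design section treats the three sequential arms together as the SUD-only condition up to 3 months, and Objective 1 compares each simultaneous arm with that condition at T1.

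**The concern.** For the comparison of types, a sequential patient's T1 score is a pre-randomisation value. It cannot carry a type effect. If the Objective 3 model is fitted as described, that score enters as an outcome under a type the patient had not yet been assigned. The same score would serve as untreated control in Objective 1 and as a PE, EMDR or ImRs result in Objective 3.

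Two features of the plan make this worth settling. The Sample size section derives the trial's size from these pairwise type comparisons, as pre-post change with 54 per arm. Its total of 162 is the same 162 that it splits into 41 sequential and 121 simultaneous patients, so sequential patients are counted in the 54. In addition, the Data analyses section plans a Bayesian assessment of the evidence for no differential effect. A contrast that is attenuated by construction would lean towards that conclusion.

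**Working it through.** **Inputs.** From Sample size: f = 0.15, alpha = 0.0167, power = 0.85, within-person correlation 0.60, 54 per arm, sequential to simultaneous 1:3. From Randomization and procedure: first-stage probabilities of 1/4, second-stage probabilities of 1/3. Assumption, not in the document: the type difference is the same at every visit after PTSD treatment.

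**1. The protocol's own figure.** For a two-group, two-measurement interaction test, lambda = f² × N × 2 / (1 − rho), referred to a noncentral F with 1 and N − 2 degrees of freedom. With N = 108: lambda = 0.0225 × 108 × 2 / 0.40 = 12.15, power 0.852. With N = 106, power is 0.844. So 54 per arm is reproduced.

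**2. Sequential share of each type pool.** (1/4 × 1/3) / (1/3) = 25%, or about 13.5 of 54, leaving about 40.5 simultaneous.

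**3. Pooled contrast at T1.** 0.75 × delta + 0.25 × 0 = 0.75 × delta, so f becomes 0.15 × 0.75 = 0.1125. Then lambda = 0.01266 × 108 × 2 / 0.40 = 6.83 and power is 0.574. About 95 per arm (N = 190) would be needed to get back to 0.85.

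**4. T1 with simultaneous patients only.** No dilution, about 40 per arm (N = 80): lambda = 0.0225 × 80 × 2 / 0.40 = 9.0, power 0.709.

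**5. Overall effect.** With equal weight on T1, T2 and T3, (0.75 + 1 + 1) / 3 = 0.917 of the true difference.

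**6. Check under the planned covariate adjustment.** f = 0.15 corresponds to a difference in change of 2 × 0.15 × √(2 / 0.40) = 0.671 SD of change. The SD of change is √(2 × 0.40) = 0.894 outcome SD, so the difference is 0.60 SD of the outcome. I simulated baseline-adjusted comparisons with 40 simultaneous and 14 sequential patients per arm, correlation 0.6 between all visits, a type effect of 0.60 SD and no timing term. The gap between patients with and without PTSD treatment at T1 is not given in the documents, so I varied it from 0 to 0.8 SD.

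| Contrast | Estimate (true 0.60) | Power at alpha 0.0167 |
|---|---|---|
| T1, pooled | about 0.45 | about 0.65 (gap 0) to 0.51 (gap 0.8) |
| T1, simultaneous only | 0.60 | about 0.81 |
| T2, pooled | 0.60 | about 0.93 |
| T3, pooled | 0.60 | about 0.92 |
| Mean of T1–T3, pooled | 0.55 | about 0.985 |
| Mean of T2–T3, pooled | 0.60 | about 0.986 |

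Putting the 0.917 factor into the two-measurement formula of step 1 gives power 0.776. That figure ignores the precision gained by averaging three visits, so the table is the better guide to the overall effect.

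**The case against.** The strongest reply is that Objective 3 never names T1. The Design section and Objective 1 define these T1 scores as the SUD-only condition, and type is assigned only afterwards, so the authors may never have meant to count them by type. Visit coding may also be settled in a document not shown here. This stands in part: the inclusion of T1 is a reading, not an explicit statement. But the article does fix the covariate, the fixed effect, the pooling and the time structure, and it limits visits for Objective 2 and not for Objective 3. Followed as printed, T1 is in.

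It can also be said that Objective 3 is worded as exploratory, with no directional hypothesis, and that differences between the Objective 1 coefficients already give undiluted T1 type contrasts. Both are true. Yet it is listed among the primary objectives and sets the sample size, and those coefficient differences are not what Objective 3 says it will report.

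A reader might go further and infer that all type comparisons shrink towards zero, or that only an analysis aligned to the start of PTSD treatment gives a pre-post change for all 54 per arm. The documents do not support that. By T2 the PTSD-treatment window has closed for everyone, so T0 to T2 and T0 to T3 are pre-post contrasts for the whole pool. Patients do differ in time since treatment at those visits, but type is allocated equally within each timing. The mix is therefore balanced across types in expectation, and averaging over it is the stated aim.

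**Conclusion.** The point holds for T1 and, mildly, for the overall effect. As printed, the pooled T1 type contrast estimates 75% of the true difference. Its power falls from 0.85 to about 0.57 on the protocol's formula, and is about 0.51 to 0.65 with baseline adjustment, depending on the assumed treated-untreated gap. The overall effect is attenuated by about 8% with almost no change in power. The contrasts at 6 and 9 months are sound.

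The 25% share follows from the allocation alone. The 92% figure assumes a constant post-treatment type effect and equal weighting of visits, and the power figures take the planned f = 0.15 as the true difference after treatment. This calls for a stated restriction of visits before analysis. It is not evidence that the head-to-head comparison as a whole is underpowered or biased.

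**What to change.** State the visits for Objective 3, in one of two ways:

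- remove sequential patients' T1 scores from the Objective 3 outcome, so that any T1 type contrast uses simultaneous patients only; or
- limit the pooled type contrasts and the overall effect to 6 and 9 months, as Objective 2 already does.

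In either case add timing (simultaneous or sequential) as a fixed effect.

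This needs no new data. Under the first option the T1 contrast rests on about 40 per arm, with power about 0.71 on the protocol's formula or about 0.81 with baseline adjustment at 0.60 SD. Under the second it is not reported. The 6- and 9-month average keeps power of about 0.986 in the simulation above.

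Re-indexing visits to the start of PTSD treatment, with the pre-treatment CAPS-5 as covariate, could be added as a sensitivity analysis. It is not required, and it would mix baselines taken before and after three months of SUD treatment.
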